#### **9.3.5 Cautions for use**

- 1) Do not operate the device except by authorized personnel and medical personnel.
- 2) Install in a location that is not adversely affected by air pressure, temperature, humidity, wind, sunlight, air containing salts, ions, etc.
- 3) To avoid the risk of electrical shock, this device must only be connected to a supply with a protective earth ground.
- 4) Mutual interference from nearby high-frequency generating electronic medical devices may cause inoperability.
- 5) Keep a distance of at least 15 centimeters between you and the irradiator.
- 6) During light irradiation, the subject wears safety glasses for eye protection.
- 7) Do not move the device during device motion.
- 8) Immediately stops the operation of the device when an abnormality is detected in the subject and takes appropriate action to ensure the subject is safe.
- 9) Prevents the subject from touching the device while it is in motion.
- 10) Not blocking the fan holes in the instrument's light irradiator.
- 11) It can be affected by conducted and radiated noise, and to minimize interference, other devices

and the

Use from a distance of at least 1 meter.

12) When cleaning the device, wipe only the surface of the device and do not use a spray sanitizer.

### 9.3.6 About control (SHAM) devices and how to use them

The control device is a device with the same geometry as the test device, with the light irradiation part consisting of LEDs of 12 mW/cm^2 or less.

to look similar to the light beam irradiated by the test device, and other appearance and operation

The method is the same as for the tester.

#### 9.3.6.1 Control (sham) device appearance

[figure not shown]

**Figure 16.** Sham device appearance

#### 9.3.6.2 Controller performance

- Output: 12 mW/cm^2
- Time: 25 minutes

### 9.3.7 Combination Therapy

In principle, the simultaneous use of other medical devices or medicines that may affect the efficacy, safety, and product performance of the investigational medical device during the clinical trial period is prohibited; however, if the use of other medical devices or medicines is unavoidable due to the treatment of subjects and ethical circumstances, the details of the use

should be recorded. In the **case of pressure ulcers, continuous wound disinfection** is **essential for conservative treatment of chronic wounds**. If disinfection is excluded, the wound may deteriorate and cause harm to the patient.

Therefore, all subjects participating in the study (both control and experimental) will continue to be disinfected daily with a 1% Silver Sulfadiazine + Foam formulation based on national guidelines for pressure ulcers published in 2019.

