### **7.2 Subject's Exclusion Criteria**

- (1) Pregnant and nursing women
- (2) Prior hip surgery
- (3) Recurrent pressure ulcers
- (4) People with osteitis
- (5) Isolated with resistant strains
- (6) Unable to be in the supine position for more than 30 minutes
- (7) People who need to take immunosuppressants or steroids for a medical condition.
- (8) Have a light sensitivity (such as photosensitivity) or are taking medications related to light.
- (9) Any other person who, in the opinion of the investigator, is unable to properly conduct the study.

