#### **10.3.2 Visit 2 (D1 ± 2 days)**

Recheck the selection criteria and exclusion criteria before irradiation, then judge the suitability and assign the subject number.

Medical examination and measurement of vital signs

Measures area assessment, Braden scale, and NRS

- ④ Phototherapy performed.
  - ⑤ Performed bacterial identification and histologic examination
- Checked medical history and medications.
- ⑦ Check for adverse events.

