### **11.2 Cautions for use**

- Do not shine the light directly into your eyes. Shining the light into your own eyes, shining it into the eyes of others, looking at it through a magnifying glass, or looking at its reflection in a mirror can cause temporary impairment of your eyes, and prolonged exposure can be harmful to your eyes.
- People with light-sensitive bodies or those taking related medications may be harmed by this product, so please consult a professional before using it.
- When using this product, you must follow the instructions in the user manual.

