### **12.2 Elimination Criteria**

- Record whether all subjects in the study have completed the study, and if irradiation or observation has been stopped, record the reason. For subjects in an ongoing clinical trial, the study may be discontinued in the following cases
  - Violation of inclusion and exclusion criteria
  - Use of prohibited medications during the treatment period: steroids, immunosuppressants
  - If a subject has a serious adverse event, or if the subject requests to discontinue the study due to an adverse event, or if the investigator believes that the adverse event warrants discontinuation of the study.
  - Subjects with systemic disease that was not detected by pre-study testing.

- The subject or the subject's legal representative due to unsatisfactory treatment effectiveness during the clinical trial.

If a proxy asks to stop the test

- Violation of the protocol by the investigator or subject.
- Subject withdraws consent to participate in a clinical trial
- If a subject can't be tracked
- If you're having trouble irradiating your subjects
- The development of any other condition requiring immediate medical attention that, in the opinion of the investigator, makes it inappropriate for you to proceed with the study.

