#### **14.6 Reporting adverse events**

- 1) Severity of adverse events: Allows you to indicate mild, moderate, severe, etc. in the adverse event report card.
- 2) Causality with an investigational medical device: Determine causality based on the evaluation criteria and display it in the adverse event record table.
- 3) Treatment: Allows you to display in the record table if there is a change in the clinical trial method, such as a change in the method of use, a decrease in the number of uses, or a discontinuation of use due to an adverse event.
- 4) Treatment course: Allows you to describe the disappearance or worsening of an adverse event due to treatment after the event occurred.
- 5) Investigator's view: Allows you to record the investigator's view of an adverse event.

**14.7 Reporting method:** This information is reported in accordance with the regulations on medical device clinical trials and the standard work instructions prescribed by the medical device clinical trial center.

- 1) An adverse event is any unintended symptom, manifestation, or disease that occurs in a subject during a clinical trial, and should be recorded in the case report based on the medical findings and severity of the adverse event and the evaluation of the causal relationship with the investigational medical device. Therefore, the criteria for evaluating the causal relationship between an adverse event and an investigational medical device should be presented.

- 2) Safety criteria refers to the criteria for assessing the severity of predicted adverse events and adverse events as they should be assessed and recorded in the case record.
- 3) Safety evaluation methods are statistical analysis methods and evaluators for the comparative evaluation of adverse events, adverse medical events, and the frequency of adverse events associated with investigational medical devices between test and control groups.

Presented quasi-.

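### If a light-related drug becomes unavoidable after D1, section 9.3.7 asks only that it be recorded; nothing requires irradiation to pause because of the drug

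*Protocol*

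**What the plan says.** **At entry.** Exclusion 7.2(8) covers subjects who "Have a light sensitivity (such as photosensitivity) or are taking medications related to light". Section 10.3.2 repeats the eligibility check once, at D1: "Recheck the selection criteria and exclusion criteria before irradiation".

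**Named hazard.** Section 11.2 states that "those taking related medications may be harmed by this product, so please consult a professional before using it". The note to subjects under 16.2 (item 2) advises care with photosensitising medicines and foods, names burns as a possible result, and lists drug classes.

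**During treatment.** Section 9.3.7 first sets a general rule: use of other devices or medicines "that may affect the efficacy, safety, and product performance of the investigational medical device during the clinical trial period is prohibited". It then makes an exception. If use of other devices or "medicines is unavoidable due to the treatment of subjects and ethical circumstances, the details of the use" should be recorded. It says nothing about irradiation in that case.

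**Discontinuation.** Section 12.2 opens with "For subjects in an ongoing clinical trial, the study may be discontinued in the following cases". The only drug-related ground reads "Use of prohibited medications during the treatment period: steroids, immunosuppressants".

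**Changes in use.** Section 14.6 item 3 provides for noting a changed method of use, "a decrease in the number of uses, or a discontinuation of use due to an adverse event".

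**The concern.** At the door, the protocol treats a light-related drug as sufficient reason to withhold the device, whatever the state of the skin. Once a subject is enrolled, the same drug leads only to a record when its use cannot be avoided. A site that follows the plan to the letter may therefore go on irradiating someone it would have refused to enrol, in the active arm at the fixed maximum of 90 mW/cm² for 25 minutes.

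The situation can be foreseen from the protocol alone. Section 9.2.1 describes antibiotic therapy as part of the standard care given in the trial, and the drug list under 16.2 opens with quinolones and tetracyclines, both antibiotic classes. Section 10.2 has bacteria identified from the D1 tissue sample, in subjects who agree to the biopsy, with results after about 7 days. An antibiotic may thus be started or changed in the middle of treatment.

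At stake is the safety of individual subjects and equal handling of the two arms. No estimate or test in the analysis is put in doubt.

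**Working it through.** The protocol states no figure on this point to reproduce. The check is a reading of every rule that could stop irradiation, followed by a count of the sessions concerned.

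**1. What triggers each control, and what does it require?**

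| Place | Trigger | What it requires |
|---|---|---|
| 7.2(8), 10.3.2 | Drug in use at screening or D1 | Not enrolled |
| 9.3.7, general rule | Avoidable use of a medicine that may affect safety | Prohibited |
| 9.3.7, exception | Unavoidable use | Record the details |
| 9.3.5 item 8 | Abnormality detected in the subject | Stop the device |
| 11.2 | Taking a related medicine | Consult a professional before use |
| 12.2 | Steroids or immunosuppressants; also criteria violations, protocol violations, adverse events, investigator's opinion | Discontinuation is possible |
| 14.6 item 3 | Adverse event | Record any reduction or stop |
| Note under 16.2, item 2 | Photosensitising medicine or food | Take care |
| Note under 16.2, item 12 | Discomfort | Stop use |

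After D1, the rules that do stop the device respond to a sign, a symptom or an event. The rules that respond to the drug itself ask for a record, a consultation or caution. No row makes a pause follow from unavoidable use of the drug.

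**2. How many sessions lie after the last eligibility check?**

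Section 10.1 places Visits 2 to 13 on D1, 3, 5, 8, 10, 12, 15, 17, 19, 22, 24 and 26.

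- Sessions in the treatment weeks: 4 weeks × 3 = 12.
- Sessions after the D1 recheck (Visits 3 to 13): 13 − 3 + 1 = 11.
- If a drug were started when the culture is reported, D1 + 7 = D8, which is Visit 5. Sessions from there on: 13 − 5 + 1 = 9.

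The table in 10.1 also marks device application at Visit 14, but 10.3.4 lists none, so that visit is left out. These are counts of sessions to which the gap could apply, not counts of exposed subjects.

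**3. Would the medication check catch a new drug?**

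Yes. Sections 10.3.2 to 10.3.4 list a medication check at every visit from 2 to 14. But no action is attached to what the check finds.

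**4. Can the subject-note list serve as the definition of a light-related drug?**

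Not as it stands. It includes sulfa drugs, while 9.3.7 has every subject in both arms treated daily with 1% silver sulfadiazine. The protocol does not say whether that topical agent counts. A hold based on the uncorrected list could stop irradiation for everyone.

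**The case against.** **The protocol already has a policy: caution plus clinical judgement.** Avoidable use is prohibited. The note to subjects addresses combined use directly. Section 11.2 calls for professional advice and for following the user manual, which is not among the documents. Section 12.2 lets the investigator stop on several general grounds, and the frequent medication checks would bring a new drug to light quickly. All of this stands, so it would be wrong to say that the protocol has no control. What remains is that every route for unavoidable use is discretionary or waits for a sign of trouble, whereas 7.2(8) leaves nothing to judgement on the same drug at entry. It is also unclear that a drug begun after valid enrolment violates an entry criterion.

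**The text is a rough translation, so the permissive verb in 12.2 should not carry much weight.** That is fair. But even if 12.2 were read as mandatory, its drug ground names only steroids and immunosuppressants.

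**A reader might infer from 10.3.3 that irradiation is given before anyone asks about medication,** since phototherapy is item 3 and the medication check item 4. The documents do not support this. Only the screening visit (10.3.1) is said to run in the listed order. At Visit 2 the tissue tests are listed after phototherapy, although 10.2 requires them immediately before treatment. List order is therefore not shown to be time order, and no number of sessions given before the check can be derived from it.

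**A hold has a price.** Missed sessions lower the delivered dose in a trial that aims for 16 evaluable subjects per arm. This is true and belongs in the cost. The alternative that 12.2 offers, discontinuation, gives up more.

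**Conclusion.** The point holds as a minor safety correction. For unavoidable use of a light-related drug after D1, the protocol requires a record and leaves everything else to caution, discretion or a reaction to symptoms. No provision makes irradiation pause because of the drug, although the same drug bars entry. The gap spans 11 of the 12 treatment-week sessions.

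The conclusion rests on the protocol text alone and assumes that the user manual, which is not available, does not itself impose a hold. The protocol gives neither a rate of photosensitiser use nor a burn risk by wavelength or dose, so nothing is claimed about how often harm would occur or how serious it would be.

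**What to change.** 1. **9.3.7:** state that irradiation, active or sham, is held while a photosensitising drug is in use, unless a non-photosensitising alternative is chosen, and that visits and assessments continue during the hold. Applying the rule to both devices protects the blind. Continued assessment keeps observed week 4 values, where a dropout would be analysed by last observation carried forward under 12.3.
2. **Definition:** have the sponsor's clinicians specify which drugs count, and state explicitly whether the mandated topical silver sulfadiazine is exempt. The hold cannot work without this. The list under 16.2 should not be taken over unreviewed.
3. **12.2:** add light-related drugs to the named medications, for consistency with 7.2(8). This alone would not pause irradiation.
4. **10.3.3:** state that the medication check is completed before irradiation and triggers the hold. This is a clarification, not the repair of a demonstrated wrong sequence.

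**Cost:** a sentence or two in 9.3.7, a few words each in 12.2 and 10.3.3, and a short drug definition. No visit, test or subject is added. The downside is that a few subjects may miss sessions and receive less than the planned dose.

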## 10 Observation items · Clinical examination items and observation methods

### 10.1 Clinical trial timeline

| Visit                                                                             | スク
Lining | Therapist             |                       |                        |                         | Monitoring  |             |
|-----------------------------------------------------------------------------------|--------------|-----------------------|-----------------------|------------------------|-------------------------|-------------|-------------|
|                                                                                   | Visit
1   | Visit 2-4
(Week 1) | Visit 5-7
(Week 2) | Visit 8-10
(Week 3) | Visit 11-13
(Week 4) | Visit
14 | Visit
15 |
| Viewpoint
(± 2 days)                                                           | D0           | D1,D3,D5              | D8,D10,D12            | D15,D17,D19            | D22,D24,D26             | D29         | D210        |
| Clinical trial
description                                                     | ○            |                       |                       |                        |                         |             |             |
| Obtaining
informed
consent and
screening
numbers
Give arcs         | ○            |                       |                       |                        |                         |             |             |
| Conformance
determination
(selection
/Exclusion
Criteria)             | ○            |                       |                       |                        |                         |             |             |
| Demographics                                                                      | ○            |                       |                       |                        |                         |             |             |
| Medical history
(past medical
history, surgical
history,
Drug Dosing) | ○            | ○                     | ○                     | ○                      | ○                       | ○           |             |
| Pregnancy test
(fertility
for women)                                        | ○            |                       |                       |                        |                         |             |             |
| Medical exams
and
Vital signs                                               | ○            | ○                     | ○                     | ○                      | ○                       | ○           | ○           |
| Annulus and
Braden scale
side
正                                          | ○            | ○                     | ○                     | ○                      | ○                       | ○           | ○           |
| Measuring pain
scores                                                          | ○            | ○                     | ○                     | ○                      | ○                       | ○           | ○           |

|                                                                    |                       |                                                 |                       |                       |                       |                       |                       |
|--------------------------------------------------------------------|-----------------------|-------------------------------------------------|-----------------------|-----------------------|-----------------------|-----------------------|-----------------------|
| Laboratory tests1 (blood tests, urinalysis f)                      |  |                                                 |                       |                       |                       |  |                       |
| Laboratory tests2 (pelvic X-ray)                                   |  |                                                 |                       |                       |                       |                       |                       |
| Medical Device Applications                                        |                       |                            |  |  |  |  |                       |
| Laboratory tests3 (fungal culture, tissue biopsy)                  |                       | 
(Proceed with D1 only) |                       |                       |                       |  |  |
| Recheck selection criteria/exclusion criteria                      |                       | 
(D1 Advance            |                       |                       |                       |                       |                       |
| Suitability determination and subject identification numbers Grant |                       | 
(Proceed with D1 only  |                       |                       |                       |                       |                       |
| Investigating adverse events                                       |                       |                            |  |  |  |  |                       |

## 10.2 Observations and clinical test items

- **Patient consent, screening number assignment, and demographic** survey: Before entering the study, the purpose and content of the study will be explained in detail to the subject, written consent will be obtained, a screening number will be assigned in the order of receipt of written consent, and demographic information will be collected. The following information will be recorded: whether or not written consent was given and the date of consent, subject's initials, gender, date of birth, address, and contact information.
- **Determine eligibility and assign a subject identification number:** If all of the subject inclusion criteria are yes and all of the subject exclusion criteria are no, the subject is determined to be eligible and assigned a subject identification code.
- **Medical history:** A detailed investigation and recording of the subject's medical history through a questionnaire and check of past medical records during the screening visit. This includes past history of diabetes, hypertension, surgery, medications, etc.
- **Medical examination:** A medical examination is performed at each visit, and any significant findings are recorded in the Medical Examination section of the case record,

and if significant medical findings that meet the definition of an adverse event are noted after study initiation, they are recorded in the Adverse Event case record. However, undesirable medical events that occurred prior to study initiation should be recorded in addition to the current medical history section.

- **Vital signs:** Checking the subject's vital signs at each visit, including temperature, blood pressure (systolic, diastolic), and pulse rate.
- **Wound assessment:** The investigator will assess the size (width×length×depth), color, presence of necrotic tissue, discharge, odor, microvascular bleeding, and granulation tissue formation of the pressure ulcer at each treatment visit.
- **Erythema: Asymptomatic (0 points), mild (1 point), moderate (2 points), and severe (3 points).**
- **Urticaria: Rate as asymptomatic (0 points), mild (1 point), moderate (2 points), or severe (3 points).**
- **Blisters: asymptomatic (0 points), mild (1 point), moderate (2 points), and severe (3 points).**
- **Measure the Braden Scale**, an indicator of pressure ulcer risk, with six items (sensory perception, skin moisture, activity level, positioning, nutrition, friction, and shear) to determine a score (1-4 points for each item, for a maximum of 24 points).
- **Numeric Rating Scale ( NRS): A tool for assessing a patient's pain.**

**Express it on a scale of 1 to 10. This is measured by asking the patient to rate their pain from 0 for no pain to 10 for unbearable pain.**

- **Other inspections**

■ **Pregnancy test:** A pregnancy test is performed on women of childbearing age at the screening visit to confirm that the subject meets the inclusion and exclusion criteria, and the pregnancy is recorded in the case record.

■ **Laboratory test 1:** Laboratory tests are performed to confirm that subjects meet the selection and exclusion criteria, and the test items are as follows. If the test was performed within 2 weeks, it can be replaced.

✓ **Blood tests:** CBC, ESR, CRP, biochemistry, etc. are performed at screening, Visit 14, and normal test values and clinical significance are recorded in the case notes.

CBC - WBC, Hb, Platelet

Electrolyte - Sodium(Na), Potassium(K)

Chloride(CL), BUN, Creatine, AST, ALT, Protein

Albumin, Total Bilirubin, Glucose

ESR, CRP

✓ **Urinalysis:** performed at screening, Visit14, with normal values and clinical significance documented in the case record.

